**Figure 1 figure1:**
[figure not shown]
Schedule of enrollment, interventions, and assessments related to the experimental study (cluster randomized trial).

### Statistical Methods

#### Estimation of Sample Size for the Experimental Study

We estimated that an optimal sample of 3000 students (about 40 schools) should be recruited in order to detect as statistically significant at the 5% level a risk ratio intervention to control of 1.10 based on the primary outcome (never smoker in the ninth grade). The estimation is based on the following assumptions: desired power 80% or higher; design effect due to the cluster design 1.98, an average cluster size of 50, and an intraclass correlation coefficient of 0.02; prevalence of the outcome in the minimal intervention (control) group 0.70; eligible students at baseline (never smoke) 92%; attrition between seventh and ninth grade 20%; and ratio intervention to control 1:1.

#### Data Analysis

Data from the trial will be analyzed primarily according to an intention-to-treat approach, preserving the random assignment [28]. Missing outcome information because of attrition at follow-up will be addressed by means of sensitivity analyses including last observation carried forward; best- and worst-case scenario, assuming missing answers as representing either the best or the worst outcome; and multiple imputation if a missing at random assumption for the missing data will not be dismissed [29].

Secondary analyses will be conducted per protocol, thus including only students in schools that adhered to at least 80% of the whole assigned intervention. Furthermore, an as-treated analysis will be conducted, comparing the outcome among students exposed to different components and intensities of the intervention, in particular the adoption of the core component *child-adult agreement* (research question 6). These approaches disregard randomization, therefore they are prone to producing biased estimates of the effect unless adjusted for most of the potential confounders [30]. However, they may be useful in order to assess the consistency between an expected effect and the intervention’s theoretical rationale [30] and in order to gain insights on the reasons for not detecting the estimated effect [31].

Finally, we will be able to compare the prevalence trends across 3 school years as well as the final prevalence at the end of follow-up between schools participating in the experimental study and schools in the external reference group, carrying on usual health education. This will enable us to estimate the potential impact of the intervention when released.

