#### Experimental Design

A parallel cluster randomized controlled experiment will be conducted with schools as units of randomization and individual students as unit of analysis. A superiority approach will be employed for hypothesis testing (ie, the null hypothesis to be rejected will be that the Tobacco-free Duo comprehensive intervention is either inferior or equivalent to the education-only component). Through this design, questions 1 to 5 will be addressed (Tables 1 and 2). The trial was registered (ISRCTN 52858080) on January 4, 2019 (ie, after enrollment of the first participant but prior to baseline assessments being completed).

**Table 1 table1:** Evaluation questions.

Objective–question		Formal question definition	

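### Two of the sensitivity analyses for attrition are badly fixed: last observation carried forward does not suit a never-smoked outcome, and multiple imputation hangs on a condition the data cannot decide

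*Protocol article*

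**What the plan says.** The Data Analysis section makes intention to treat the primary approach and leaves attrition to sensitivity analyses: "Missing outcome information because of attrition at follow-up will be addressed by means of sensitivity analyses including last observation carried forward". The same sentence adds a best- and worst-case scenario, which carries no condition, and then "multiple imputation if a missing at random assumption for the missing data will not be dismissed".

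The sample-size section sets the scale: "attrition between seventh and ninth grade 20" percent, "prevalence of the outcome in the minimal intervention (control) group 0.70", and a target of "a risk ratio intervention to control of 1.10 based on the primary outcome (never smoker in the ninth grade"). It counts as eligible the 92% of students who have never smoked at baseline. Table 2 defines the outcome as a negative answer on ever having tried smoking, even a few puffs. Table 3 schedules a baseline in the fall of grade 7 and follow-ups at the end of grades 7, 8 and 9, with guardian questionnaires at the same time points.

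**The concern.** Ever smoking is an absorbing state. A student who reports it at follow-up 1 or 2 and then leaves is a known failure at grade 9, and carrying that report forward is exact. A student who leaves as a never smoker still has one to three years of onset risk ahead, at the ages the program targets, and carrying forward sets that risk to zero. The plan itself expects 30% of controls to start by grade 9.

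The error is one-sided within each arm. It pulls the arms together when attrition is equal and pushes them apart when attrition differs. Differing attrition is possible here: schools and students are unblinded, and only the full-program arm has contracts, membership cards, yearly disclosure and a lottery.

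The condition on imputation is a separate fault. Observed data cannot distinguish missing at random from missing not at random, and the article states no criterion. The one listed method that makes principled use of the intermediate waves could therefore be kept or dropped after the data are seen.

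**Working it through.** **Inputs from the sample-size section.** Control never-smoking 0.70; risk ratio 1.10, so intervention 0.70 × 1.10 = 0.77 and a target difference of 7.0 points; attrition 20%; 3000 students, of whom 92% are eligible; design effect 1 + (50 − 1) × 0.02 = 1.98, which matches the stated value.

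**Assumptions (not in the protocol).** Waves at about 0, 9, 21 and 33 months, read from the Table 3 schedule; constant onset rate; one third of dropouts last seen at each of the first three waves; dropouts have the same onset as completers (missing at random) unless stated otherwise.

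**Share of dropouts last seen as never smokers.** S(t) = p^(t/33), where p is never-smoking at grade 9.

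| Arm | S(0) | S(9) | S(21) | Mean q | True grade-9 value |
|---|---|---|---|---|---|
| Control | 1 | 0.907 | 0.797 | 0.901 | 0.70 |
| Intervention | 1 | 0.931 | 0.847 | 0.926 | 0.77 |

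Carrying forward scores control dropouts as 90% never smokers where 70% is right.

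**Equal attrition.** Arm rate under carrying forward = (1 − a) × p + a × q, with a the attrition.
- Control: 0.8 × 0.70 + 0.2 × 0.901 = 0.740
- Intervention: 0.8 × 0.77 + 0.2 × 0.926 = 0.801
- Difference: 6.1 points instead of 7.0; risk ratio 1.08 instead of 1.10

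The dropout pattern sets the range. If all dropouts were last seen at baseline (q = 1), the rates are 0.76 and 0.816, a difference of 5.6 points. If all were last seen at follow-up 2, they are 0.719 and 0.785, a difference of 6.6 points.

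**Unequal attrition, no true effect.** Take p = 0.70 in both arms and an assumed 25% v 15% attrition.
- Arm losing 25%: 0.75 × 0.70 + 0.25 × 0.901 = 0.750
- Arm losing 15%: 0.85 × 0.70 + 0.15 × 0.901 = 0.730
- False difference: 0.10 × (0.901 − 0.70) = 2.0 points, or 2.0/7.0 = 29% of the target effect

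The range is 0.10 × (0.797 − 0.70) = 1.0 point (all last seen at follow-up 2) to 0.10 × (1 − 0.70) = 3.0 points (all last seen at baseline).

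With 2760/2/1.98 = 697 effective students per arm, the standard error of the 2.0-point difference is √[(0.750 × 0.250 + 0.730 × 0.270)/697] = 0.0235. A nominal two-sided 5% test would then reject in about 14% of trials.

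**What remains if imputation is dropped.** At 20% attrition:

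| Scenario | Control | Intervention | Risk ratio |
|---|---|---|---|
| All missing best | 0.76 | 0.816 | 1.07 |
| All missing worst | 0.56 | 0.616 | 1.10 |
| Control best, intervention worst | 0.76 | 0.616 | 0.81 |
| Control worst, intervention best | 0.56 | 0.816 | 1.46 |

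Carrying forward (0.740 v 0.801) lies close to the all-best row and adds little to it. The crossed extremes, 0.81 to 1.46 around a target of 1.10, are too wide to show whether a result is robust.

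**The case against.** The best defence is that these are sensitivity analyses, not the main estimate, and that the same sentence lists best- and worst-case scenarios, which need no missing-at-random assumption and score dropouts as failures in one scenario. That is correct. It means the plan already has outer bounds; it does not make carrying forward informative, and the bounds are wide.

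Second, under the only attrition figure in the protocol, taken as equal by arm, carrying forward merely dilutes the effect, which is conservative for a superiority trial. This also stands: the false effect needs attrition, or the mix of dropouts, to differ by arm, and the 25% v 15% split is an assumption. The Data Collection and Management section also promises to trace students who change school and to reach absentees at home, which may lower attrition, although the plan still budgets 20%.

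Third, not dismissing missing at random may mean a judgement of plausibility rather than a test on the data. That is a fair reading, but no criterion is given, and imputation would be useful as one scenario whichever way the judgement fell.

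Four stronger readings are tempting and are not supported:
- **All dropouts are scored as successes.** Only those last seen as never smokers are.
- **The primary analysis is complete-case.** The article does not say how missing outcomes enter the primary analysis, nor that earlier smoking reports are discarded. An analysis plan that is not shown may settle this.
- **Imputation must therefore be the primary estimate.** This does not follow, for the same reason; standard imputation also rests on missing at random.
- **The false effect reaches 3.3 points if dropouts have twice the onset rate.** With completers at 0.70 in both arms, carrying forward shows 0.730 v 0.718, or +1.2 points, while the true difference is 0.6475 − 0.6685 = −2.1 points; 3.3 is the gap between the two, not an effect created from none. If both true arm rates are instead held at 0.70, completers must be 0.770 v 0.737, so a complete-case analysis shows the same 3.3 points and carrying forward is not the cause.

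**Conclusion.** The point holds for two of the listed sensitivity analyses. Carrying forward is unsuited to an outcome that can only be lost: it dilutes a true 7.0-point effect to about 6.1 points at 20% attrition in both arms (5.6 to 6.6 by dropout pattern). At an assumed 25% v 15% split with no true effect and data missing at random, it creates about 2.0 points (1.0 to 3.0) in favour of the arm losing more students. These sizes rest on a constant onset rate and assumed wave timing; the central values also assume dropout spread evenly over the waves. The condition on multiple imputation cannot be decided from the observed data, and if it is invoked nothing credible is left between the extremes. This should be changed, but it does not show that the primary analysis is wrong.

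**What to change.** In the Data Analysis section:
1. Replace last observation carried forward by carrying forward reported ever smoking only; leave the other missing grade-9 outcomes missing.
2. Run multiple imputation of those outcomes without the missing-at-random condition, using the baseline, follow-up 1 and 2 and guardian data, with an imputation model that respects school clustering.
3. Add a delta-adjusted analysis for data missing not at random, in which dropouts have a higher onset than imputed and the shift may differ by arm.
4. Keep best and worst case as outer bounds.

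The cost is a change of wording and a little more analysis work. The data are already scheduled for collection in Table 3.

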### Ethics and Dissemination

#### Ethics Approval and Consent to Participate

The study was approved by the Regional Ethics Review Board, Umeå (registration number 2017/255-31). Participant schools and individuals were required to give explicit informed consent to data collection, analysis, and reporting prior to inclusion in the study. Written and verbal operator-recorded consent has been obtained from parents or guardians of participating minors. The procedure approved by the Ethic Review Board included verbal and even opt-out consent.

## Results

Recruitment of schools started in the fall of 2017 and continued until June 2018. In total, 43 schools were recruited to the experimental study, and 16 schools were recruited to the observational study. Data collection started in the fall 2018 and is ongoing. The last round of data collection is planned for the spring 2021. Data analysis of baseline characteristics is due to commence, and first results are expected at the end of 2020.

## Discussion

This study protocol, for the evaluation of a complex intervention for the universal prevention of tobacco use initiation among early adolescents, proposes a mixed methods approach, combining the reciprocal strengths of a randomized experiment and of observational studies, as well as primary and secondary analyses of both study designs.

The protocol has several strengths, compared to similar studies. First, it aligns with the current increasing consensus on the importance of mixed methods [32] and of triangulation approaches in accruing robust evidence in the evaluation of interventions [33-35]. Two aspects of community trials call for triangulation approaches. On the one side, experiments establish the effect of being randomized to specific conditions, which in pragmatic trials do not coincide necessarily with the receipt of the intervention [31]. By conducting an as-treated analysis [30] according to the actual implementation of and adherence to the intervention, we aim to triangulate the question of effectiveness of Tobacco-free Duo program. By comparing groups no longer randomly assigned to the levels of the intervention, this analysis will have to take bias from confounding into account.

On the other side, participants in an experiment (be they organizations or individuals) constitute an imperfect representation of the underlying populations on which the inference should be drawn, because of the numerous selection steps involved in the conduction of an experiment [36]. In this study, we plan to include a comparison group that comprises schools that agreed to participate in annual surveys among all students in the 3 final compulsory grades but did not agree to be randomized to either experimental group. These schools are likely to well-represent the majority of Swedish schools (ie, the subgroup consisting of those that would not adopt the intervention if offered it at the scaling-up stage). By comparing the development over time of tobacco use in these schools with that of schools randomized to the minimal or comprehensive intervention (across a set of school-level characteristics), we aim to infer the added effect of the intervention on decline in tobacco uptake. For instance, if the prevalence of lifetime smoking or tobacco use similarly declines in reference group schools as in the randomized ones, we may project that the impact of a large and intensive dissemination of the intervention (even if effective in the randomized comparison) would be minimal.

Furthermore, we propose the use of qualitative methods and of process data in order to achieve 2 additional objectives. The first objective to be pursued is a deeper understanding of how the conduction of the intervention may differ between school organization characteristics. This knowledge is important in order to judge cluster-level confounding in nonrandomized studies [37]. An additional advantage of such a piece of knowledge would be the possibility to make projections of the potential benefits deriving from the application of the method to large communities with a known distribution of the studied characteristics.

The second objective is to study the occurrence and the nature of undesirable side effects connected with the intervention when delivered as intended. While it is recognized that such effects are of importance in the study of medical or psychological treatments, much less attention has been devoted to methods for studying them in the domain of preventive interventions. One of the reasons behind this failure is the need to carefully conceptualize expected adverse outcomes in a logic framework (one cannot study all kind of potential outcomes). According to the framework presented by Lorenc and collaborators [27], we will focus on potential adverse effects connected with the core component of the intervention (ie, the adult-child agreement) in terms of psychological and equity adverse effects. Children not able to be supported by an adult may be particularly vulnerable for reasons that may or may not be connected to the target behavior. The publicity around the contract among peers and the presence of fringe benefits for those complying may increase the segregation of these psychosocial risks. Also, children whose adult partners “infringe” the agreement by starting or relapsing into smoking may experience a profound disappointment and loss of trust that undermines the relation with a significant other.

The third strength of this study protocol rests in the choice of a standardized comparison group in the randomized controlled trial design. Several community trials employ comparator conditions that are largely opportunistic (ie, rely upon the concept of usual conditions). While undoubtedly pragmatic, this approach may be misleading at the stage of judging on causal effects deriving from the application of an intervention that is the explicit scope of a randomized controlled trial. In fact, while the alternative intervention under investigation is often quite standardized, usual conditions are not, even if in a certain context (for instance, in a given school system), there may be some recurrent features. To clump together different conditions without any knowledge of their potential effects or even of their content may lead to biased results in any direction [38]. It is purported that the advantage of usual conditions would be to represent the background reality of which the actual participants would be a valid representation [37]. Anyone who has conducted experimental studies is aware that this is far from being true, rather the opposite. Participants in studies (be they experimental or not) are usually a nonrepresentative sample of the background populations (individuals or organizations), both because of the application of explicit inclusion and exclusion criteria and because of self-selection.

When the Tobacco-free Duo program started in the early 1990s, there was a limited amount of research on decision support and public commitments as components of public health interventions; the latter was mainly investigated among adults [18]. Since then, there have been some advancements in knowledge regarding intervention models including decision support and public commitment among young people, but this knowledge must still be regarded as insufficient. The proposed study will, therefore, add substantially to the empirical evidence in this regard.

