#### Nonexperimental (Observational) Design

Two different comparisons will be established. In the first comparison (addressing objective 2 question 6) an as-treated analysis of the trial data will be conducted where individual students assigned to the Tobacco-free Duo intervention and signing a child-adult contract will be contrasted to students receiving other Tobacco-free Duo components but not signing the contract. In the second comparison (addressing objective 3 question 7), all students attending schools in grades 7 to 9 in both experimental groups will be contrasted to students in a convenience sample of schools in the same broad catchment areas where the experiment takes place (an external reference group). Schools in this external reference group will be those willing to participate in the survey data collection but not in the experimental study. Therefore, they will represent the subset of schools in the target areas that will probably not be willing to adopt the program once released for dissemination. In Table 2, a summary is presented of the relevant comparisons established with an observational design.

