### Study Procedures

#### Invitation and Selection of Schools

All schools located in 11 regions of central and south Sweden encompassing the higher block grades (7 to 9) will be invited to participate in the study through a letter addressed to the school’s headmaster at the end of the school year preceding the conduction of the intervention. We estimate this underlying source sample as about 600 schools. Schools will be eligible if they have at least 2 classes in the target grades and if they did not or do not plan to adopt the Tobacco-free Duo program until the evaluation is completed. The eligibility criteria will be assessed among respondents willing to participate through a questionnaire on school organization and characteristics sent concurrently with the invitation.

The final selection will rest on a formal agreement issued by the school headmaster to be randomly assigned to the intervention or comparator condition, to engage the school personnel in the training for and in the delivery of the intervention, and to facilitate the data collection. We estimate that at least 40 schools will be recruited into the experimental study.

Schools not willing to be randomized will be asked if they are willing to participate as part of the external reference group (ie, to deliver and report on the usual antismoking program if any and to collect data from students in repeated anonymous cross-sectional surveys).

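### A comparison with 16 self-selected reference schools cannot, without strong unstated assumptions, estimate the program's impact on release or discount a positive randomised result

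*Protocol article*

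**What the plan says.** Nonexperimental (Observational) Design describes the reference group as "a convenience sample of schools in the same broad catchment areas where the experiment takes place". It is made up of schools willing to be surveyed but not to join the experiment, and the section concludes that "they will represent the subset of schools in the target areas that will probably not be willing to adopt the program". The Discussion widens this: "These schools are likely to well-represent the majority of Swedish schools". The same sentence explains that majority as the schools that would decline the program at scale-up.

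Two uses follow. Data Analysis, on comparing prevalence trends and final prevalence between trial and reference schools, states: "This will enable us to estimate the potential impact of the intervention when released". The Discussion then gives an example of interpretation: if lifetime smoking or tobacco use falls similarly in reference and randomised schools, the impact of wide dissemination may be projected as minimal, even when the randomised comparison shows the program to be effective.

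Later the Discussion also says: "Participants in studies (be they experimental or not) are usually a nonrepresentative sample of the background populations". It gives self-selection as one of the reasons.

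**The concern.** The impact of releasing a program falls on the schools that take it up. To estimate it, one needs to know what those schools would have experienced without it. By the protocol's own description the reference schools are probable non-adopters, and they chose to be surveyed but not randomised. Their trend can stand in for that of adopting schools only if the two kinds of school would have moved in parallel. The protocol neither states nor defends that assumption.

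The funder commissioned the evaluation to inform possible national recommendations (Introduction). As written, a non-randomised contrast could be used to discount a positive randomised result, or a favourable one could be reported as impact for most Swedish schools. In either case school self-selection would be read as program effect.

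**Working it through.** The protocol gives no sample size, precision or bias figure for this comparison, so there is none to reproduce.

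**Inputs**
- Randomised schools: 43 (Results, "43 schools were recruited to the experimental study").
- Reference schools: 16 (Results, "16 schools were recruited to the observational study").
- Source: 11 regions of central and south Sweden (Invitation and Selection of Schools, "We estimate this underlying source sample as about 600 schools").
- Planned control prevalence of never smoking 0.70 and risk ratio 1.10 (Estimation of Sample Size).
- Whole-school anonymous surveys at the end of school years 1, 2 and 3 (Table 3).

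**1. Coverage.** Assume that all 59 recruited schools come from the 600. That count precedes eligibility screening, so the shares are approximate.
- Not randomised: 600 − 43 = 557. Reference share: 16/557 = 2.9% (16/600 = 2.7% of all source schools).
- In neither part: 600 − 43 − 16 = 541, and 541/600 = 90%.

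**2. Whom the 16 schools represent.** Methods limits them to a subset of schools in the target areas, whereas the Discussion extends them to the majority of Swedish schools. They passed two filters: they declined randomisation and they accepted yearly surveys. The Discussion's remark on nonrepresentative participants expressly covers non-experimental studies.

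**3. Declining randomisation versus declining the program.** Joining the trial meant accepting either arm, committing staff to training and delivery, and supporting data collection. A school could refuse that package and still want the program. The Intervention overview reports about 80 municipalities that have implemented it, with adoption at the request of regional government, municipalities or schools.

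**4. What the contrast estimates.** Let A1 be the outcome in program schools, A0 the outcome those schools would have had under usual practice, and R the outcome in reference schools.

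A1 − R = (A1 − A0) + (A0 − R)

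The first term is the program effect and the second is self-selection. A0 is never observed, because both trial arms receive at least the manualised education. The same split applies to changes over time, where the second term becomes the difference in underlying trends.

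**5. Illustrative size.** The planned effect is 0.70 × 1.10 = 0.77, or 7 points. It is borrowed here only for scale, since it refers to ninth-grade never smoking against education-only. Let b be the advantage of the reference schools over A0 (in a trend analysis, the advantage in change). The apparent effect is 7 − b.

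| b (points) | apparent effect (points) |
|---|---|
| 0 | 7 |
| 2 | 5 |
| 3.5 | 3.5 |
| 5 | 2 |
| 7 | 0 |

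A negative b inflates the effect: b = −3.5 gives 10.5. The protocol gives no basis for choosing b.

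**6. The override reading.** A similar decline means only that the two terms in step 4 roughly cancel or are both near zero. If the randomised comparison is positive, the arms differ, so reference schools cannot match both. If they match the full-program schools, they outdo education-only schools by the randomised effect. Then either manualised education did worse than usual practice, or the schools differ. Neither shows that dissemination would achieve little.

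**7. Timing.** The first whole-school survey comes at the end of year 1, after the program has started, so pre-program trends cannot be compared. Grades 8 and 9 in year 1 are only a partial baseline.

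**The case against.** The strongest reply is that this is an exploratory objective, labelled non-experimental and worded with hedges. The comparison is to be made across school-level characteristics, and the Discussion also seeks knowledge of school organisation in order to judge cluster-level confounding. Reference schools report their usual programs, and they are the only usual-practice data in the study. Asking whether smoking is falling anyway is sensible.

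Much of this stands, and it is why the comparison should be kept. It does not support the two uses made of it. Adjustment handles measured differences, but willingness to be randomised separates the groups completely: every trial school had it and the reference schools did not.

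A reader might infer more than the document supports:

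- **That majority and non-adopters contradict each other.** They do not, since the Discussion sentence equates them. The problems are the step from target areas to Sweden and the step from declining randomisation to non-adoption.
- **That the Discussion's warning about usual conditions condemns this comparator.** That warning concerns comparators in randomised trials whose content is unknown, and these schools report theirs. Only the remark on nonrepresentative participants carries over.
- **That any level difference between school types would swamp the result.** Question 7 concerns decline over time, and a constant gap would largely cancel in a trend comparison. It would still affect the final-prevalence comparison, which Data Analysis also lists. Differing trends remain the issue for the former.
- **That 43/600 = 7.2% is the adoption rate, so that 7 points shrink to about 0.5 across all schools, too small for the comparison to detect.** The ratio measures willingness to join a trial. Past and planned adopters were ineligible, and the 600 precedes eligibility screening. The diluted figure is also not what a contrast between participating schools estimates, so setting it against that contrast's precision compares unlike quantities.
- **That the reference data are useless.** They remain informative as description.

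**Conclusion.** The concern holds in a limited form. Without strong unstated assumptions, chiefly that reference and adopting schools would have had parallel trends under usual practice, the comparison cannot estimate impact on release, represent most Swedish schools or override the randomised result. That conclusion rests on the protocol's own text and on the decomposition above. The actual bias is unknown in size and direction, and the 7-point illustration shows only how much a given difference would matter.

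The effect is confined to objective 3 (question 7) and the dissemination projection. The wording should be changed before results are interpreted.

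**What to change.** - **Discussion:** delete or qualify the sentence containing "These schools are likely to well-represent the majority of Swedish schools" and its equation of declining randomisation with declining the program. Remove the reading that a similar decline shows minimal impact even if the program is effective in the randomised comparison.
- **Data Analysis:** replace "This will enable us to estimate the potential impact of the intervention when released" with a statement that reference-school trends will be reported descriptively as context under usual practice, adjusted for the school-level characteristics collected and with those characteristics tabulated beside the trial schools'. State that no causal or national impact inference will be drawn.
- **Any rollout projection:** present it as a labelled scenario, namely the randomised effect across an assumed uptake range. Say that this effect is the full program's increment over education-only, not its benefit over usual practice. Do not use 43/600 as an adoption rate.

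The cost is wording, one table and, if wanted, a simple scenario calculation; no new data are needed. The downside is a more modest claim for objective 3.
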